## Abstract

**Background:**

Insomnia is the most common sleep disorder. Repetitive transcranial magnetic stimulation (rTMS) is safe and effective for insomnia disorder (ID). Convergent evidence show that the medial prefrontal cortex (mPFC) may be involved in the regulation of sleep and awakening at the cortical level and may serve as a potential target of rTMS in the treatment of ID. The purpose of this clinical trial is to study the efficacy of mPFC-rTMS in the treatment ID and explore the neural mechanism using resting-state functional magnetic resonance imaging (fMRI).

**Methods and design:**

This will be a parallel-group randomized, patient- and assessor-blinded trial. The study will recruit 60 ID patients assigned to a real mPFC-rTMS group or a sham mPFC-rTMS group. The allocation ratio is 1:1, with 30 subjects in each group. Interventions will be administered five times per week over a 4-week period, with an 8-week follow-up period. All participants will undergo neuropsychological and fMRI evaluations. The primary outcome measure of this study is the change scores of the Pittsburgh Sleep Quality Index (PSQI). The secondary outcome measures include the fMRI measurements, the Hamilton Depression Scale (HAMD), the Hamilton Anxiety Scale (HAMA), a sleep diary, and a polysomnography. Assessment of all parameters will be performed at baseline, post-treatment, and during follow-up.

**Discussion:**

It is expected that the study results will provide strong evidence of the effectiveness and the neural mechanism by which mPFC-rTMS improves sleep quality in ID patients.

**Trial registration:**

Chinese Clinical Trials Register ChiCTR2100054154. Registered on 10 December 2021.

## Introduction

Insomnia is the most common sleep disorder [1]. Due to the increase in social pressure and aging population, the prevalence of insomnia will continue to increase [2]. A recent meta-analysis of the prevalence of insomnia disorder (ID) in the general population in China showed that the prevalence rate of ID is 15.0% [3]. The long-term existence of insomnia may be the cause of the huge social and economic burden of this disease and can lead to cognitive dysfunction, psychological abnormalities, and increased suicide tendency [4]. Therefore, early identification and early effective therapies for ID patients are especially important.

At present, the first-line therapies for insomnia recommended by sleep guidelines are cognitive behavioral therapy and hypnotic medication. However, many insomniacs have poor compliance with cognitive behavioral therapy in clinical practice, and long-term use of hypnotic medication also has side effects and increase suicide risks. In recent years, there have been an increasing number of novel physical methods to treat insomnia, such as repetitive transcranial magnetic stimulation (rTMS), which has emerged as a new option due to its low side effects.

As a neuromodulation technique, the common therapeutic target of rTMS is the dorsolateral prefrontal cortex (DLPFC). Many studies [5–7] applied rTMS (on right DLPFC, 1 Hz) for insomniacs, and the results indicated that rTMS can improve the sleep quality of insomniacs and the effect is better than hypnotic medication without side effects. These results suggest that rTMS is safe and effective for primary insomnia.

Huang et al. [8] choose the posterior parietal lobe as the stimulated position for insomnia patients with generalized anxiety. They showed that the anxiety and insomnia symptoms were improved significantly. However, some studies suggest that rTMS does not significantly improve insomnia symptoms in Parkinson’s disease [9]. A recent meta-analysis suggested that rTMS was effective in ID patients, while the placebo effect of sham stimulation was significant [10].

The aforementioned studies are focused on the right DLPFC or posterior parietal cortex with low-frequency rTMS. Although rTMS display a certain effect, but there are still some patients who cannot benefit from it. The current studies did not involve abnormal brain network of insomnia patients as a stimulation target; then in this study, we will explore the therapeutic effects and neural basis of another new stimulated target.

Insomnia is an abnormal sleep pattern. Two important neurotransmitter receptors (dopamine receptors and adenosine receptors) involved in sleep arousal are expressed in the nucleus accumbens (NAc) [11, 12]. In addition, the glutamate neurons of the thalamus paraventricular nucleus and the ventral tegmental area can control awakening by regulating the NAc [13, 14]. Therefore, the NAc may play an important role in regulating sleep and awakening. Lazarus et al. [15] proposed a network model of sleep-wake regulation, suggesting that adenosine and dopamine receptors in NAc regulate sleep-wake behavior through cortical activation, mainly involving the excitatory neural projection from the medial prefrontal cortex (mPFC) to NAc. In addition, mPFC can directly project excitatory neurons downward to the sleep-wake regulatory system such as tuberopapillary nucleus of hypothalamus, lateral hypothalamus, and locus blueleus. These results suggest that mPFC may be involved in the regulation of sleep and awakening at the cortical level and may serve as a potential target of rTMS in the treatment of chronic insomnia.

Two recent neuroimaging studies used functional magnetic resonance imaging (fMRI) to analyze the resting state functional connection (RSFC) of NAc in ID patients and revealed abnormal RSFC between NAc and mPFC which suggest the brain related to the severity of insomnia [16, 17]. Shao et al. [16] proposed an abnormal NAC-mPFC circuit in ID. In addition, the hypothalamus, a central role in sleep-wake regulation, was recently used as the seed for functional connection by fMRI, and the results showed that the bilateral hypothalamus and bilateral mPFC resting state functional connection were enhanced in ID patients and were positively correlated with sleep quality [18]. Moreover, neuroimaging revealed reduced gray matter density [19, 20], abnormal regional homogeneity (ReHo) [21], amplitude of low-frequency fluctuations (ALFF) [22], and reduced activation of mPFC [23, 24]. These studies suggest that mPFC may play an important role in the pathophysiological mechanism of insomnia.

Therefore, we hypothesized that 1-Hz rTMS stimulation over mPFC would improve insomnia symptoms of ID patients by altering mPFC seed functional connectivity in the group receiving real mPFC-rTMS group compared with the sham mPFC-rTMS group.

## Methods/design

### Objective

The study objectives are (1) to determine the efficacy of mPFC-rTMS for ID and (2) to elucidate the neural mechanisms for the effects of mPFC-rTMS on ID.

### Trial design

This study is designed as a prospective parallel-group, patient- and assessor-blinded, randomized controlled single-center clinical trial with two parallel groups to detect the superiority of real mPFC-rTMS over the sham mPFC-rTMS. Digital randomization table will be performed as block randomization with a 1:1 allocation assigned to either a real mPFC-rTMS group or a sham mPFC-rTMS group. The neuropsychological measurements, a 1-week sleep diary, a 1-day polysomnography (PSG), and fMRI scans will be performed at baseline, post-treatment (immediately after completion of the 20-day treatment), and 8 weeks follow-up (8 weeks after the last session). The detailed flowchart is shown in Fig. 1. The trial will be conducted in accordance with the SPIRIT reporting guidelines [25]. Ethical approval has been granted by the ethics committee of Zhenjiang mental health center (202007), and the trial is registered at ChiCTR (CHiCTR2100054154).

**Fig. 1 Fig1:**
[figure not shown]
Flow chart of the study. PSQI, Pittsburgh Sleep Quality Index; HAMD, Hamilton Depression Scale; HAMA, Hamilton Anxiety Scale; PSG, polysomnography; fMRI, functional magnetic resonance imaging

### Sample size

This study aims to determine the efficacy and brain mechanism of mPFC-rTMS in ID patients. Based on preliminary experiments, the PSQI score significantly decreased by 4.43 ± 3.60 in the group treated with mPFC-rTMS compared to 1.30 ± 2.58 in the control group. Based on a power analysis, 26 patients per group were required to detect a significant difference (power = 0.9, *α* = 0.05, two-sided). Thus, considering a 15% dropout rate, we plan to recruit 30 patients per group to compensate. As to fMRI research, there is no known sample size calculation. However, for the exploratory study, 15 to 30 patients are adequate to test the null hypothesis [26].

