### Outcome

#### Primary outcome

Our primary outcome will be the mean change scores of insomnia severity assessed using PSQI from baseline to the end of the treatment period. The PSQI is a 19-item insomnia assessment tool consisting of seven component scores, including sleep quality, sleep latency, sleep duration, sleep efficiency, sleep disorders, hypnotic medication, and daytime dysfunction. The higher score reflects the worse sleep quality.

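### The stated 26 per group is not what the planned t test needs on the pilot figures (23), and 30 per group falls half a patient short of 26 after 15% dropout; both slips are minor and the trial stays adequately powered

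*Protocol article*

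**What the plan says.** The Sample size section of the Protocol article rests on preliminary data in which the PSQI score "decreased by 4.43 ± 3.60 in the group treated with mPFC-rTMS compared to 1.30 ± 2.58 in the control group". From these it concludes that "26 patients per group were required to detect a significant difference", with power 0.9 and a two-sided alpha of 0.05. It then says: "considering a 15% dropout rate, we plan to recruit 30 patients per group to compensate". It refers to a power analysis but names neither a test nor a formula.

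Three other places bear on the calculation. The abstract gives the group sizes: "The allocation ratio is 1:1, with 30 subjects in each group". The Primary outcome section defines the endpoint as the "mean change scores of insomnia severity assessed using PSQI from baseline to the end of the treatment period", so the pilot decreases and their SDs are on the scale of the primary outcome. The Statistical analysis section plans independent t tests between the groups, paired t tests within each group, and a repeated-measures analysis of variance.

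**The concern.** The section prints everything that a two-group comparison of means needs: two means, two SDs, the power, the alpha and the sidedness. A reader can therefore repeat the calculation. With the t test that the article itself plans, the answer is not 26. The next step, from 26 to 30, is also not the calculation that keeps 26 patients when 15% are lost.

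What is at stake is accurate reporting, not the viability of the trial. The figures 26, 90% and 15% are likely to be repeated in the results paper as the justification of the sample size. As printed, they do not describe what the planned test delivers with 30 per group.

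**Working it through.** **Inputs, from Sample size unless noted**

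- Real group: mean decrease 4.43, SD 3.60. Control group: mean decrease 1.30, SD 2.58.
- Power 0.90, alpha 0.05, two-sided.
- Dropout 15%, 30 recruited per group; 1:1 allocation (abstract).
- Between-group test: independent t test (Statistical analysis).

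**Step 1. Effect size**

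- Difference = 4.43 − 1.30 = 3.13.
- Pooled SD for equal groups = √((3.60² + 2.58²)/2) = √((12.96 + 6.6564)/2) = 3.132.
- d = 3.13/3.132 = 0.999.

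**Step 2. Can the stated 26 be reproduced?**

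Normal approximation: n = 2(z₀.₉₇₅ + z₀.₉₀)²/d² = 21.04, so 22 per group.

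t test, from the noncentral t distribution: n = 22.05, so 23 per group. The Welch version also gives 23, with 91.1% power.

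| n per group | Power, t test |
|---|---|
| 22 | 89.9% |
| 23 | 91.2% |
| 25 | 93.3% |
| 26 | 94.2% |
| 30 | 96.8% |

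The stated 26 is thus 3 above the t-test answer, and its power is about 94%. Variants (normal approximation, then t test where two figures are given):

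| Variant | n per group |
|---|---|
| One-sided, 90% power, pooled SD | 18 |
| Two-sided, 80% power, pooled SD | 16, 17 |
| Two-sided, 95% power, pooled SD | 27, 28 |
| Two-sided, 90% power, larger SD (3.60) | 28, 29 |
| Two-sided, 90% power, smaller SD (2.58) | 15, 16 |
| Two-sided, 95% power, simple mean of the SDs | 26, 27 |
| Two-sided alpha 0.025, 90% power, pooled SD (normal only) | 25 |
| Rank test, minimum relative efficiency 0.864 | 22.05/0.864 = 25.5, so 26 |

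The rank-test row is the only one that reaches 26 with the stated power, alpha and sidedness unchanged. The article does not mention it. The row for 95% power with averaged SDs reaches 26 only by the normal approximation and by departing from the stated power.

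**Step 3. The dropout allowance**

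- The printed figure: 26 × 1.15 = 29.9, so 30. This reproduces the 30.
- The number that leaves 26 after 15% loss: 26/(1 − 0.15) = 30.6, so 31.
- What 30 leaves: 30 × 0.85 = 25.5 per group, or 60 × 0.85 = 51 in total against 2 × 26 = 52.

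**Step 4. What the design delivers with the planned t test**

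- Requirement 23, allowing for dropout: 23/0.85 = 27.1, so 28 per group. The planned 30 exceeds this.
- With 25 completers per group, power at the pilot effect is 93.3%.
- 30 per group still leave 23 with up to 1 − 23/30 = 23.3% dropout.

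**The case against.** The strongest reply is that the article names no test for its power calculation, so 26 need not be an error. A Wilcoxon-Mann-Whitney calculation with the conservative efficiency of 0.864 gives exactly 26 from the same effect, alpha and power: 89.4% power at 25 per group and 90.6% at 26. That stands as far as it goes. The documents do not support saying that no valid calculation yields 26. They support only that 26 is not the answer for the t test, which is the between-group test that the article plans. Nothing shows that a rank test was used. Another route to 26 is 22/0.85 = 25.9, which would mean that dropout was allowed for twice; the document cannot confirm that either.

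A second reply is that a condensed article may leave the choice of test to the full protocol or SAP. That is fair, and the silence alone is no fault. The point is that the inputs and the result are both printed and do not match under the analysis that is also printed.

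A third reply is that the dropout gap is half a patient per group, or one patient in 52. That is correct; it would not be worth raising alone.

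A reader might also infer that the trial is underpowered, or that its figures flatly contradict one another. Neither follows. A requirement above the minimum is conservative and is compatible with a 90% target, and only the step from 26 to 30 conflicts with itself, by that half patient. Whether the pilot effect is optimistic is a separate question. Power at smaller differences or larger SDs says nothing about this arithmetic, and the article gives no basis for choosing such values.

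**Conclusion.** The point holds as a minor correction to the sample-size statement. On the pilot figures and the planned two-sided t test, 23 per group are required, so the stated 26 is 3 higher and corresponds to about 94% power. The dropout step uses a multiplier of 1.15 where division by 0.85 is needed, which leaves 25.5 instead of 26. Neither slip leaves the trial short of power: at the pilot effect, it has about 93% power with 25 completers per group and 97% with 30.

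This rests on three assumptions: that the power calculation was meant for the independent t test on PSQI change, that the two pilot SDs are pooled with equal weight (Welch gives the same 23), and that the pilot effect is taken at face value. If a rank-based calculation was intended, 26 is valid for that test, and what remains is the mismatch with the planned analysis and the half-patient gap.

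**What to change.** Keep 30 per group and restate the paragraph for the planned test. For example: with a difference of 3.13 and a pooled SD of 3.13 (d = 1.00), 23 patients per group give at least 90% power with a two-sided 5% independent t test; 30 per group leave about 25 after 15% dropout, which gives about 93% power at the pilot effect.

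If 26 came from another test or another SD, name it and keep the figure, but state that about 25 per group, not 26, remain after 15% dropout.

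The cost is one paragraph. The recruitment target and the planned analysis do not change.

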### Participants and recruitment

We will post recruitment information in the hospital to recruit participants who report clinically significant insomnia. Prior to recruitment, the investigator will inform participants of the benefits, as well as possible risks (poor therapeutic effects and adverse events associated with rTMS) in the study. Informed consent will be obtained by investigators. All participants will sign informed consent forms before collecting data and randomization. Investigators will also sign the informed consent forms and record the informed consent process in the medical records.

Investigators will decide whether the participants meet the inclusion criteria based on the scores of PSQI, HAMD, and HAMA. The eligible participants will complete a baseline rs-fMRI, a 1-week sleep diary, and a 1-day polysomnography (PSG). All participants who satisfy the inclusion criteria will be randomly divided into either a real mPFC-rTMS group or a sham mPFC-rTMS group in a ratio of 1:1.

#### Inclusion criteria

Participants who comply with all the following criteria will be enrolled in the clinical trial:Aged 18–65Meeting the diagnostic criteria for insomnia disorder according to the Diagnostic and Statistical Manual of Mental Disorders, Fifth EditionPSQI score > 11 points, HAMD-14 score < 7, HAMA score < 14, and HAS score > 32Sign informed consent forms for this studyHave not received medications for anxiety, depression, or insomnia within 4 weeks prior to enrollment in the studyNo history of staying up late and shift in the past 4 weeks

#### Exclusion criteria

Participants who comply with one or more of the following criteria will be excluded from the clinical trial:Having a family history of mental illness or other mental illnessA history of alcohol and drug abuseInsomnia caused by other sleep disorders such as sleep apnea syndrome and restless legs syndromeSerious medical diseases including the cardiovascular system, nervous system, urinary system, respiratory system, digestive system, and other serious physical diseasesPregnant or breastfeeding womenReceived physical therapy such as rTMS, transcranial direct current stimulation, or electroshock in the last monthsContraindication for MRI including claustrophobia, abnormal signal, or obvious asymmetrical head structure by MRI

### Oversight and dissemination

#### Composition of the coordinating center and trial steering committee

A monitoring/steering/safety committee will not be set up for this study. The study management team will be responsible for the organization of the trial including identifying potential recruits and obtaining informed consent and data collection. The study management team will meet at the beginning, the interim, and the end of the trial to monitor the study regularly to ensure adequate recruitment rate, data accuracy, and data validity.

#### Composition of the data monitoring committee, its role, and reporting structure

The study management team will be responsible for the ongoing management of the trial. In addition, we have the original medical records, and the Zhenjiang Health and Family Planning Commission will conduct a regular assessment. No data monitoring committee is needed.

#### Dissemination plans

The results of this trial will be published in a peer-reviewed journal.

#### Randomization, allocation concealment, and blinding

The eligibility participants will be randomly assigned to either a real or a sham mPFC-rTMS group with a 1:1 allocation. This study will use the Statistical Analysis Software (version 9.3, SAS Institute Inc., Cary, NC, USA) to generate the random allocation sequence. The list of randomization will be closed in computer-generated opaque envelopes with sequence numbers printed on the outside of the envelopes. After researchers screened the eligible patient, the envelopes will be opened by the researchers. The unblinded researchers will generate the allocation sequence and assign participants to interventions. The trained operators who operate rTMS will not be blinded to allocation and therefore will be excluded from assessments and data processing. Participants, statistical analysts, and assessors will be blinded. Unblinding should only be performed in case of an emergency, such as any serious adverse events.

#### Intervention

The subjects will be prohibited from receiving any other relevant treatments including drugs that can improve sleep during the trial period. *There are concomitant medications such as medications for anxiety, depression, or insomnia that are prohibited during this trial*. All relevant treatments and compliance will be recorded in the case report form. We attempted to improve adherence to interventions by strategies (i) emphasizing to participants the importance of their attendance at follow-up assessments even if they were no longer compliant with the intervention; (ii) during the follow-up period, investigators will be arranged to respond to patient inquiries; (iii) investigators will contact patients 2 (± 1) days before each visit via letters and telephone contact; and (iv) providing training in issues related to compliance for all study investigators who will contact the participants.

#### Real mPFC-rTMS group (shown in Fig. 2)

All operators who operate mPFC-rTMS will receive training to ensure consistent rTMS technique on all participants. Deep transcranial magnetic stimulation (dTMS) was administered using a Magstim Rapid2 TMS stimulator (Magstim, Whitland, UK) with H7 coil (Brainsway, Jerusalem, Israel). The front rim of the helmet was fixed at 1 cm above the nasion, then the treatment location of the H7 coil stimulates mPFC bilaterally. Before the first treatment session, single-pulse TMS was delivered to measure the resting motor threshold (RMT) of the extensor halusis brevis muscle of the participant’s toes. RMT was defined as the minimum intensity, which elicited 3 motor evoked potential (MEP) responses in 6 attempts. Treatment parameters were 1 Hz, 5-s stimulation, and 1-s stimulation intervals with a stimulation intensity of 80% of RMT. The number of repetitions was 200, the total number of pulses was 1000, and the total stimulation time was 20 min. The real mPFC-rTMS therapy will be performed 1 time per day 5 days per week for 4 weeks.

**Fig. 2 Fig2:**
[figure not shown]
Enrollment schedule, treatment, and outcome measures. PSQI, Pittsburgh Sleep Quality Index; HAMD, Hamilton Depression Scale; HAMA, Hamilton Anxiety Scale; PSG, polysomnography; fMRI, functional magnetic resonance imaging

#### Sham mPFC-rTMS group (shown in Fig. 2)

The sham mPFC-rTMS group will be delivered by a single helmet with sham coils. The sham coil is designed to induce similar noise and scalp sensations with the same parameters as the active stimulation group.

#### Functional MRI scanning procedure

The resting-state fMRI data will be obtained at Zhenjiang Mental Health Center with a Philips 3.0-T MRI scanner. All fMRI images will be acquired from a gradient echo-echo plane imaging under the following parameters: 30 slices, repetition time (TR) = 2000 ms, echo time (TE) = 30 ms, thickness = 5 mm, field of view (FOV) =240 × 240 mm, flip angle = 90°, matrix size 64 mm × 64 mm, and total 185 volumes. Participants will be required to stay awake, keep their eyes closed, not move, close their eyes, and not try to think about anything. The real and sham mPFC-rTMS groups will be examined three times (baseline, post-treatment, and follow-up).

